**Specific Aim 3: To evaluate whether the effects of CBCT depend on the timing of program delivery.**

The change in mean score on empathic accuracy and resilience measures from before to after receipt of the CBCT program among participants in the early-start group (from T0 to T1) will be compared to the change in mean score on empathic accuracy and resilience measures from before to after receipt of the CBCT program among participants in the delayed-start group (from T2 to T3)**.**

**Specific Aim 4: To evaluate whether CBCT-informed interventions improve patient outcomes.**

Upon completion of their training program, chaplain residents will provide spiritual consults to patients throughout the Emory hospital system. We will conduct comprehensive assessments in order to examine whether patient (n = 300) outcomes are improved for those receiving chaplain spiritual care augmented by CBCT, in comparison to those receiving spiritual care from chaplains who receive CBCT later in their residency. To this end, study personnel will shadow chaplain residents in both groups and will administer self-report assessments of negative symptomology (depression, anxiety, and loneliness) and well-being (quality of life, hope) to consented patients. In addition, study personnel will audio record chaplain-patient interactions. Patient outcomes will be gathered from retrospective chart reviews and will include use of opioid pain medication, duration of stay, patient’s denial of care, and patients’ Press Ganey satisfaction scores.

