Participants will be approached by a researcher who will explain the study to them and have them sign an informed consent document if they understand the study component and are interested in participating. Chaplain resident participants will receive the CBCT as part of their clinical pastoral education (CPE) curriculum. Chaplain resident participants will receive the CBCT either in the first educational unit (the early-start group) or approximately midway through the residency year (the delayed-start group). Residents in the early-start group will meet virtually for a didactic approximately every two weeks to discuss their residency experience in the context of their CBCT knowledge and caregiving approach. Residents in the delayed-start group will meet for a similarly structured and scheduled didactic on spiritual health topic(s) unrelated to patient care. After the delayed-start group receives CBCT approximately midway through the residency year, the students in the delayed-start group will also meet virtually for the CBCT-focused didactic to discuss their residency experience in the CBCT context and the early-start students will receive the spiritual health didactics on topic(s) unrelated to patient care. All didactics will be 1.5 hours in length. All chaplain resident participants will view the empathic accuracy video and complete the questionnaires at four times during the residency year: before the early-start group receives CBCT (baseline, or T0); after the early-start group completes CBCT (T1); before the delayed-start group receives CBCT (T2), and after the delayed-start group completes CBCT (T3). A subset of the chaplain residents will be interviewed at three time points relative to their training in CBCT. The interviews consist of open-ended questions to further query their learning experiences with CBCT. Researchers will compare differences in the mean scores of empathic accuracy and resiliency measures over time.

[figure not shown]

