During their training program, chaplain residents will provide spiritual consults to patients throughout the Emory hospital system. We will examine whether patient (n = 300) outcomes are improved for those receiving chaplain spiritual care augmented by CBCT, in comparison to those receiving spiritual care from chaplains who receive CBCT at the end of their residency program. To this end, study personnel will shadow chaplain residents in both groups and will administer self-report assessments of negative symptomology (depression, anxiety, and loneliness) and well-being (quality of life, hope) to consented patients. In addition, study personnel will audio record chaplain-patient interactions. Patient outcomes will be gathered from retrospective chart reviews and will include use of opioid pain medication, duration of stay, patient’s denial of care, and patients’ Press Ganey satisfaction scores.

In a final step, using patient chart reviews we will examine chaplain and patient factors that may mediate the link between spiritual consults and improved patient outcomes. Specifically, we will examine whether chaplain empathic accuracy or self-reported compassion mediate the impact of spiritual care consults on patient health outcomes. We will also examine whether patients’ well-being (hope, quality of life), or negative symptoms (depression, anxiety, loneliness) mediate the impact of spiritual care consults on patient health outcomes.

We will also use the ambulatory ambulatory audio recordings of the chaplain-patient interactions to interrogate which aspects of the chaplain-patient interaction mediate improved patient outcomes (see Figure 4). Spiritual consult audio recordings will be coded by 2 trained, independent CBCT instructors for CBCT content. They will also be coded for linguistic and behavioral elements derived from existing models of compassionate interaction in the hospital environment[^9^](#_ENREF_9).

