- (15 min) **Empathic Accuracy (EA) Task**[**^8^**](#_ENREF_8)**:** a dynamic video assessment that asks subjects to continuously rate the emotions of others as they tell emotional autobiographical stories.
- (2 min) **Spiritual Meaning Scale (SMS)**[^20^](#_ENREF_20): a 15-item, likert-scale inventory that assesses the extent to which someone endorses a belief in something larger than themselves.
- (4 min) **Jefferson Scale of Empathy**[^21^](#_ENREF_21)^,^[^22^](#_ENREF_22): a 20-item scale designed to measure empathy in practicing health care professionals and health care professional students. It has been translated into 53 languages and has been used in more than 80 countries.

Total time required for completion of measures is approximately 45 minutes. All measures will be delivered digitally.

- 1. **Post Patient Consult Checklists**
- (2-4 min) **Post-Visit Checklist for CBCT:** a 41-item checklist that assesses the encounter the CBCT-trained Chaplain Resident had with the patient; including how/if the Resident prepared for the consult, assessed the patient’s state of mind, used specific tools and skills during the consult, and how well the Resident thought the encounter went.
- (2 min) **Post-Visit Checklist for non-CBCT:** a 17-item checklist that assesses the encounter the non-CBCT-trained Chaplain Resident had with the patient; including how/if the Resident prepared for the consult, assessed the patient’s state of mind, used specific tools and skills during the consult, and how well the Resident thought the encounter went.

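### The protocol gives conflicting times for the Aim 4 patient consults and for the comparison chaplains' CBCT, so an untrained comparison group is not secured

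*Protocol*

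**What the plan says.** Specific Aim 4 and the later part of Procedures (section 2, Design) describe one patient comparison, with the same 300 patients, assessments and chart outcomes. They differ on two points.

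- **When consults take place.** Aim 4: "Upon completion of their training program, chaplain residents will provide spiritual consults to patients throughout the Emory hospital system". Procedures: "During their training program, chaplain residents will provide spiritual consults to patients throughout the Emory hospital system".
- **When the comparison chaplains receive CBCT.** Aim 4: "in comparison to those receiving spiritual care from chaplains who receive CBCT later in their residency". Procedures, patient part: "spiritual care from chaplains who receive CBCT at the end of their residency program". Procedures, chaplain part: "After the delayed-start group receives CBCT approximately midway through the residency year", after which that group moves to CBCT-focused didactics. Specific Aim 1 also says about midway.

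The four chaplain assessments are fixed relative to training: T0 and T1 before and after early-start CBCT, T2 and T3 before and after delayed-start CBCT. The text ties patient enrolment to none of them.

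Under Measures, one of the two post-visit checklists "assesses the encounter the non-CBCT-trained Chaplain Resident had with the patient". Data analysis plans independent-samples t-tests and chi-square tests for patient outcomes. The Aim 5 mediation regressions include group assignment.

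**The concern.** Aim 4 asks whether CBCT-informed care improves patient outcomes. That needs some patients seen by trained chaplains and others, over a comparable period, seen by chaplains not yet trained. With every resident due to receive CBCT, only the interval from T1 to T2 has one group fully trained and the other untouched. The protocol text does not confine consults to it, and the two descriptions of consult timing disagree.

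If many comparison patients are seen by trained chaplains, a null result cannot be told apart from both groups having had the training. The Aim 5 mediation analyses inherit the problem. The Synopsis says the pilot data are to estimate efficacy and inform a randomised trial, so a diluted estimate would carry forward. Analysis cannot repair this afterwards: if patients are enrolled only once both groups are trained, data on untrained care do not exist.

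**Working it through.** **1. The texts side by side**

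| Point | Aim 4 | Procedures, patient part | Aim 1 and Procedures, chaplain part |
|---|---|---|---|
| Consults | after the training program | during it | not stated |
| Comparison group's CBCT | later in the residency | end of the residency | about midway |

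*After* and *during* conflict. *End* and *midway* conflict. *Later* agrees with *midway*, since midway is later than the first unit in which the early-start group is trained. There are therefore two contradictions, not three.

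**2. What each reading leaves of the contrast**

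Let pE and pD be the shares of early-start and delayed-start patients whose chaplain had completed CBCT by the consult. If CBCT gives the same benefit whenever it is taught, a comparison by cohort estimates (pE − pD) times the true effect. Equal benefit is an assumption; Aim 3 exists to test whether timing matters.

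| Reading | pE | pD | pE − pD |
|---|---|---|---|
| Consults after the residency | 1 | 1 | 0 |
| Consults through the year, delayed CBCT midway | 0.75 | 0.25 to 0.375 | 0.375 to 0.50 |
| Consults through the year, delayed CBCT at the end | 0.75 | about 0 | about 0.75 |
| Consults only between T1 and T2 | 1 | 0 | 1 |

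The first and last rows follow from the definitions. The middle rows are illustrations. They assume consults spread evenly over the year, early-start training complete after one quarter and, for the midway row, delayed-start training complete after five-eighths to three-quarters. The protocol gives none of these figures.

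To keep the same power, sample size grows as 1/(pE − pD)²: 1/0.75² = 1.8, 1/0.50² = 4.0, 1/0.375² = 7.1.

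**3. What dilution would do to power**

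The protocol gives no alpha, power, effect size or SD for the 300 patients, so there is no design figure to reproduce. For scale only, assume 150 per group, two-sided alpha 0.05 and independent patients. The standardised effect giving 80% power at full contrast is (1.960 + 0.842) × √(2/150) = 0.323.

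| Contrast remaining | Effect | Power |
|---|---|---|
| 1 | 0.323 | 80% |
| 0.75 | 0.243 | 56% |
| 0.50 | 0.162 | 29% |
| 0.25 | 0.081 | 11% |
| 0 | 0 | 5% (the alpha level) |

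Clustering of patients within at most 30 chaplains is ignored.

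**The case against.** The strongest reply is that an untrained comparison group is plainly intended. Aim 4 speaks of chaplains who get CBCT later, those giving the consults are still called residents, and there is a checklist for residents without CBCT. This stands as to intent, but intent does not fix the enrolment period.

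A reader might infer that Aim 4, as written, has both groups already trained. The protocol does not support that outright. It holds only if the training program means the residency, and the term is undefined. Background and the CBCT description use it for spiritual caregiver training, and Aim 3 calls the course the CBCT program, which favours the residency. But the interview text refers to training in CBCT, and a whole-residency reading sits badly with the rest of Aim 4.

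A reader might also infer that the t-tests are split by early- or delayed-start cohort. Data analysis does not name the grouping variable. It speaks of CBCT-informed consults, which could mean classification by training status, and group assignment appears only in the mediation regression. The dilution argument therefore applies if the comparison is by cohort.

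Finally, the study schematic (Figure 3) is missing from the available text and may show when patients are enrolled. The declared primary outcomes are chaplain measures, and this is a pilot. These points limit how strongly the concern can be put. They do not remove the contradictions.

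**Conclusion.** The concern holds as two contradictions, on consult timing and on when the comparison chaplains are trained, with the consequence that the text does not secure the untrained comparison group Aim 4 needs. Neither stated consult timing, followed literally alongside delayed CBCT at midway, guarantees it.

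The size is not determinable from the protocol. The remaining contrast lies anywhere from none (consults after the residency, equal benefit from early and late CBCT) to full (consults confined to T1 to T2). It would be tempting to quote the loss as half or more of the effect, or as a four- to seven-fold sample size. Those figures hold only under the assumed training dates and even accrual in the midway row above, and should not be cited as the protocol's own.

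The matter should be settled before patients are enrolled, because it decides what Aim 4 can conclude.

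**What to change.** 1. Reconcile Aim 1, Aim 4 and both parts of Procedures on when consults occur and when the delayed-start group is trained, and define the training program in Aim 4.
2. State that the main Aim 4 comparison uses consults after T1 and before delayed-start CBCT begins (T2), early-start (trained) against delayed-start (not yet trained). Tying the window to T1 and T2 makes it valid whichever delayed-start date is confirmed.
3. Record the date of every consult.
4. Analyse consults outside the window only secondarily, by the chaplain's CBCT status on the consult date, with calendar time in the model because training status and residency experience advance together.

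The cost is protocol wording and one recorded date. The downside is a shorter period for the main comparison, possibly with fewer than 300 patients. The protocol does not give the length of the T1 to T2 interval, so the sponsor should state how many patients it expects there.

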**Specific Aim 5: To explore chaplain and patient mediators of the impact of spiritual care consults on patient outcomes.**

To examine mechanisms that mediate improved patient outcomes following compassion-informed spiritual consults, chaplains will wear an ambulatory assessment device that records chaplain-patient interactions. Recordings will be coded for (1) use of, and adherence to, the CBCT-informed modules, and (2) compassion language and action. Mediation models will test whether chaplain characteristics, patient characteristics, or chaplain-patient interactions account for improved patient outcomes.

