To evaluate whether CBCT-informed interventions improve patient outcomes, descriptive statistics (means, standard deviation, standard error) will be used to characterize baseline demographics and responses to self-report assessments. All data will be evaluated for normality, and appropriate procedures will be performed in cases where normality is violated. To evaluate whether CBCT-informed spiritual consults impact patients’ negative symptoms, well-being, and patient health outcomes (duration of stay and patients’ Press Ganey satisfaction scores) we will conduct independent samples t-tests. Dichotomous variables (denial of treatment, opioid use) will be evaluated using chi square tests.

To explore chaplain and patient mediators of the impact of spiritual care consults on patient outcomes, chaplain resident, patient, and chaplain-patient interactions will be tested in mediation analyses using linear regression analysis in order to examine which factors account for improvement in patient outcomes (opioid use, duration of stay, denial of care, patient satisfaction). Any chaplain variables (empathic accuracy or self-reported compassion) that are impacted by CBCT, or patient variables (negative symptoms, well-being) that are impacted by CBCT-informed modules will be entered as independent variables into linear regression analysis with group assignment, and with patient health outcomes as the dependent variable in order to examine whether chaplain, patient, or chaplain-patient interaction variables render group assignment insignificant in accounting for variance in patient health outcomes[^31^](#_ENREF_31).

1. **Compensation:**

No compensation will be provided to participants.

1. **Risks to participation:**

Chaplain residents and Emory Healthcare patients may experience some emotional discomfort while completing the questionnaires. To minimize this risk, all participants will be informed that they are free to skip any questions that are upsetting and that they can stop the questions at any time. In addition, they will be provided help in contacting the Emory Faculty and Staff Assistance Program (FSAP).

In addition, the questionnaires that subjects will fill out as part of this study will contain personal information, and participants may have private pieces of audio recorded.

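### Adherence to the CBCT modules cannot be judged as a mediator by whether it makes group assignment non-significant, because it has no natural score in consults by chaplains not yet trained in CBCT

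*Protocol*

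**What the plan says.** Specific Aim 5 gives two families of codes for the audio recordings: "Recordings will be coded for (1) use of, and adherence to, the CBCT-informed modules, and (2) compassion language and action". It then says: "Mediation models will test whether chaplain characteristics, patient characteristics, or chaplain-patient interactions account for improved patient outcomes". The Procedures text under Design repeats that the recordings serve to find which aspects of the interaction mediate better patient outcomes, and describes the first family as follows: "Spiritual consult audio recordings will be coded by 2 trained, independent CBCT instructors for CBCT content". Neither place limits this coding to one group. Residents in both arms are observed ("study personnel will shadow chaplain residents in both groups") and their consults are recorded.

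The comparison patients in Specific Aim 4 are "those receiving spiritual care from chaplains who receive CBCT later in their residency".

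The Data analysis section fixes the method: linear regression of patient health outcomes on the candidate mediators together with group assignment, to see whether "chaplain, patient, or chaplain-patient interaction variables render group assignment insignificant in accounting for variance in patient health outcomes".

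For the chaplains' own post-visit checklists the protocol does separate the two situations. There is a 41-item form for CBCT-trained residents and, for the others, "a 17-item checklist that assesses the encounter the non-CBCT-trained Chaplain Resident had with the patient". The recording codes have no such separation.

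**The concern.** Adherence presupposes that the chaplain has the modules to follow. A chaplain who has not had CBCT can be neither adherent nor non-adherent. The variable is therefore defined by group membership, and the planned model asks whether it explains away group membership.

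That matters because the Synopsis presents this work as a search for what makes chaplaincy care effective and as preparation for a randomized trial. If adherence appears to account for the group effect only because it is nearly the same variable as group, the next trial would take forward a mechanism that the data never tested.

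Use of the modules, or CBCT content, is a milder case. It can be rated in any recording, but it is close to a measure of whether the intervention was delivered, so the same criterion says little about mechanism there too.

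**Working it through.** **Inputs.** From the protocol: 300 patients in total, up to 30 residents, and the regression and decision rule above. The protocol gives no power, effect size, score distribution or group split for the patient aims, so there is no figure of its own to reproduce. Assumed: 150 patients per group, independent patients, two-sided 5% test, total group effect detectable at 80% power, and an adherence score on a 0-1 scale with mean *m* of 0.4 to 0.8 and SD *s* of 0.1 to 0.3 in the CBCT group. In every case below the mediator has no true effect on the outcome.

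**Total effect.** (1.960 + 0.842) × √(2/150) = 0.323 SD. The expected z for group alone is 2.80, and group is non-significant in 20% of analyses.

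**Case 1: adherence missing in comparison consults.** Complete cases come from the CBCT group only. Group is then constant and identical to the intercept. The design matrix has rank 2 for 3 columns, so no group coefficient exists.

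**Case 2: adherence scored zero in comparison consults.** The correlation with group is r = (m/2) / √(s²/2 + m²/4). The variance inflation of the group coefficient is 1/(1 − r²) = 1 + (m/s)²/2. The expected z for group falls to 2.80 × √(1 − r²), and group is non-significant with probability P(|Z| < 1.96) at that mean.

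Lowest ratio: m = 0.4, s = 0.3 gives r = 0.2/√(0.045 + 0.040) = 0.69 and z = 2.80 × √(0.045/0.085) = 2.04. Highest ratio: m = 0.8, s = 0.1 gives r = 0.4/√(0.005 + 0.160) = 0.98 and z = 2.80 × √(0.005/0.165) = 0.49.

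| m | s | m/s | r with group | variance inflation | group non-significant |
|---|---|---|---|---|---|
| 0.4 | 0.3 | 1.33 | 0.69 | 1.9 | 47% |
| 0.6 | 0.3 | 2 | 0.82 | 3.0 | 63% |
| 0.6 | 0.2 | 3 | 0.90 | 5.5 | 78% |
| 0.8 | 0.2 | 4 | 0.94 | 9.0 | 85% |
| 0.8 | 0.1 | 8 | 0.98 | 33 | 92% |

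These percentages count all analyses. Counting only simulated trials in which the total group effect was significant (2,000 runs per setting), an inert score removed that significance in about 25%, 58%, 73% and 85% of them for m/s = 1, 2, 3 and 4.

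**Case 3: comparison consults score low but not zero.** This suits CBCT content better than adherence. With mean 0.6, SD 0.2 in the CBCT group, a significant group effect was lost in about 62% of simulated trials when comparison scores had mean 0.1, SD 0.1, and in about 39% with mean 0.2, SD 0.2. With all comparison scores at zero (m/s = 3) it was about 73%.

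**What the zero-scored model estimates.** Removing group from the score leaves 0 for every comparison patient and the deviation from the group mean for every CBCT patient. The adherence slope therefore comes entirely from variation within the CBCT group. The group coefficient becomes an extrapolation: the difference expected for a CBCT consult with no adherence at all. Comparison patients add nothing to what is learned about adherence.

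**The case against.** Several points on the other side are fair.

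- **Use, or CBCT content, is not undefined.** Two instructors can rate any recording as having none or little of it. A reader might infer that the whole first family of codes lacks a valid score for half the patients and that the model cannot give a between-group answer. The documents do not support that. Only adherence lacks a natural meaning in an untrained chaplain's consult. The model fails outright only if adherence is left missing there, which the protocol does not say. The even split is an assumption.
- **Adherence is not named in the regression sentence.** The variables listed for entry are chaplain and patient measures, and interaction variables appear only generically in the same sentence. This is true, but Specific Aim 5 and the Procedures text make the recording codes the interaction variables and call them mediators, so the link is in the text.
- **Scoring rules may sit in a coding manual or an SAP.** They may. The defect is not the missing scoring rule, however. The protocol itself names the code, the model and the criterion, and that combination misleads under either obvious scoring.
- **An inert mediator would usually show a non-significant coefficient of its own**, in about 95% of analyses at the 5% level. An analyst who also required that coefficient to be significant would often be protected. The criterion as worded looks only at group, and this protection is not stated. A reader should still not infer that zero scoring always looks like full mediation: at the lowest ratio in the table, group stays significant in just over half of analyses.
- **Some comparison consults may follow training.** Specific Aim 4 places the consults after the training program and the Procedures text places them during it. The comparison chaplains' CBCT is variously later, midway or at the end of the residency. Some delayed-start consults could then have an adherence score, so it is not established that the score is undefined in the entire comparison group.
- **The aim is exploratory, in a pilot.** This limits the severity but does not remove the point.

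**Conclusion.** The point stands for adherence, in a limited form. Under the stated criterion, adherence gives either no estimable group effect (missing) or a group effect weakened mainly by overlap with the score (zero). In the second case group is non-significant in 47% to 92% of analyses with no mediation present, against 20% without the variable. That range rests on the even split, independent patients, 80% power, m/s of 1.33 to 8 and zero scores throughout the comparison group. Lower ratios, or comparison scores that vary above zero, reduce it.

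For use or CBCT content the criterion is weakly informative, not invalid. Compassion language and action, and the chaplain-level and patient-level mediators, are not touched by this point. No primary outcome or treatment comparison depends on it. The change is worth making but of modest severity.

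**What to change.** Change the mediation paragraph of the Data analysis section in three respects.

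1. Analyse adherence to the CBCT-informed modules only among patients whose chaplain had already been trained in CBCT at the time of the consult. Regress the outcome on the adherence score with chaplain as a random effect, and report the result as an association. Defining trained status by consult date also requires the statements on consult timing to be reconciled.
2. Use as between-group interaction mediators only codes scored by the same rules in both groups: compassion language and action, and CBCT content if it is scored that way. Say that CBCT content mainly reflects delivery of the intervention.
3. Replace the loss-of-significance criterion with an estimate of the indirect effect and its confidence interval.

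**Cost.** Only analysis wording changes; recordings, coders and patients stay the same. Adherence would be reported as a within-group association from roughly 150 patients (300/2) and about 15 chaplains (30/2, if up to 30 residents split evenly), so it will be imprecise and not protected from confounding between chaplains. Little information is given up, since the zero-scored regression already takes its adherence slope from those patients alone.
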